### Concealment mechanism {16b}

Opaque, sealed envelopes stored in a locked safe, accessible only to the researchers responsible for the trial, will ensure allocation concealment. The sealed envelopes will be opened exclusively by the hand surgeon during the enrolment process.

### Implementation {16c}

After obtaining signed informed consent, the dedicated research nurse assigns the randomized envelope to the treating hand surgeon, who is responsible for enrolment and intervention allocation. Participants assigned to surgery are placed on the surgical waiting list by the treating hand surgeon. While the enrolling hand surgeon may perform the procedure, they will have no further contact with the participant to maintain allocation concealment. For participants assigned to patient education and exercise therapy, the hand surgeon will notify the PTs involved in the research study. The designated PTs will then contact the participant to schedule an appointment for the exercise therapy program at the clinic.

## Assignment of interventions: blinding

### Who will be blinded {17a}

Independent hand surgeons, responsible for the follow-up measurements at 3, 6, and 12 months after intervention, will remain blinded to treatment allocation. Participants in both groups will wear a Tubigrip, glove, or bandage on the wrist during all assessment visits, preventing the assessor from determining whether the participant has undergone surgery. The blinded assessor is not allowed to access the medical journal until the measurements are completed and recorded in the study protocol. After the assessment, the evaluating hand surgeon may access the medical journal, remove the Tubigrip, and discuss further treatment options with the participant, if necessary. Additionally, data analysts will also be blinded to treatment allocation.

### Procedure for unblinding if needed {17b}

We do not anticipate any circumstances that would require unblinding.

## Data collection and management

### Plans for assessment and collection of outcomes {18a}

Baseline data including demographics are collected by the hand surgeon responsible for the participant and stored in case report forms (CRF). PROMs and objective outcomes (wrist ROM and grip strength) are collected at baseline, 3, 6, and 12 months after intervention. Data on complications and the need for additional surgery or other treatments will be retrieved from the medical records.

### Plans to promote participant retention and complete follow-up {18b}

All post-enrolment appointments are provided free of charge. Participants are scheduled for regular follow-up visits to support retention. Participants who miss scheduled appointments will be contacted by phone and/or mail to reschedule. Those who are unable or unwilling to attend in-person follow-up assessments are offered the option of a video consultation. Participants who decline both in-person and video assessments are asked to complete the PROMs and return them by mail. In the event of a dropout, reasons for discontinuation will be recorded, and all data collected up to that point will be retained and analysed. Participants who withdraw after inclusion but before undergoing the intervention will be replaced. In the exercise therapy group, regular follow-ups with the treating PT will support adhering to the program and enhance retention.

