### Outcomes {12}

#### Primary outcome measure

The primary outcome is the change of PRWE score [31] with a primary endpoint at 6 months following the start of the intervention. The PRWE is a wrist-specific PROM designed to assess pain and disability in daily activities over the past week. It consists of a pain subscale (5 items) and a function subscale (10 items), with a total score ranging from 0 to 100, where a higher score indicates greater disability. The PRWE is a valid and reliable tool for assessing wrist and hand injuries [32], with strong psychometric properties in wrist OA [33]. The validated Swedish version of the PRWE will be used [34].

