#### Survival

The survival of the two treatments will be analysed at 12 months. Survival is the success of the treatment, indicated by the absence of additional surgery during the study period due to insufficient improvement or symptom recurrence. If a participant is scheduled for additional surgery, the date of enrolment on the waiting list for surgery is recorded, and survival, measured in months, will be calculated from the initiation of study treatment to that date.

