## Statistical methods

### Statistical methods for primary and secondary outcomes {20a}

For descriptive analysis, categorical data is presented as frequencies and percentages, whereas ordinal or skewed data is presented as median (IQR) and normally distributed continuous variables as mean (SD). For the primary endpoint, comparison between partial wrist denervation, and the patient education and exercise therapy program, the Wilcoxon signed-rank test will be used for paired data, and the Mann–Whitney *U*-test will be applied for unpaired data when the data are non-normally distributed or ordinal.

*T*-tests will be employed for changes in continuous data that follow a normal distribution, while the chi-square test will be used for categorical data. Normality will be assessed by the Shapiro–Wilk test. Generalized estimating equations (GEE), adjusted for age, sex, pain catastrophizing, operated dominant hand, SLAC/SNAC OA classification according to Watson and Vender [3, 4], and treatment site (Stockholm or Malmö), will be used for analysis of differences between groups regarding longitudinal data with repeated measurements. A robust estimator covariances matrix will be used. The working correlation matrix is selected according to the lowest Quasi-likelihood under Independence Model Criterion (QICC), and linear models will be used for all variables. Kaplan–Meier analysis will be performed to generate survival curves and Cox regression to compare differences in survival at 12-month post-intervention. *P*-values < 0.05 are considered significant.

Statistical analyses will be conducted following the intention-to-treat (ITT) principle. A secondary per-protocol (PP) analysis will be performed as a sensitivity analysis to assess the robustness of the findings. If a participant requires additional wrist surgery during follow-up or has a major trauma or other disease affecting the included hand, analyses will be conducted according to ITT up to that event. Data collected after such an event will not be analysed.

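### Replacing participants who withdraw between randomisation and treatment leaves them without a defined outcome and probably turns the ITT set into those who were randomised and started treatment

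*Protocol article*

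**What the plan says.** The protocol's section on retention (18b) sets the rule: "Participants who withdraw after inclusion but before undergoing the intervention will be replaced". The statistical methods section (20a) sets the analysis principle: "Statistical analyses will be conducted following the intention-to-treat (ITT) principle". A per-protocol analysis is added there as a sensitivity analysis.

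The order of events is in the allocation sections. Under Implementation (16c), "After obtaining signed informed consent, the dedicated research nurse assigns the randomized envelope to the treating hand surgeon". Under Concealment mechanism (16b), "The sealed envelopes will be opened exclusively by the hand surgeon during the enrolment process". Treatment comes later in both arms: for surgery, "Participants assigned to surgery are placed on the surgical waiting list by the treating hand surgeon"; for exercise, "The designated PTs will then contact the participant to schedule an appointment for the exercise therapy program at the clinic". No waiting time is given for either arm. The Discussion acknowledges that participants are not blinded.

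Time is counted from treatment. The primary outcome has its "primary endpoint at 6 months following the start of the intervention". Survival in months "will be calculated from the initiation of study treatment to that date". The data collection section (18a) likewise places the 3-, 6- and 12-month assessments after the intervention.

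**The concern.** ITT means that everyone randomised is analysed in the allocated arm. Withdrawal after inclusion and before the intervention falls after randomisation, at a time when an unblinded participant can know which arm was drawn. Leaving at that point can depend on the arm. Someone waiting for surgery may improve or change their mind; someone allocated to exercise may leave because surgery was what they wanted. Adding other people restores the head count but not the comparison that randomisation created.

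At stake is selection after randomisation in the primary comparison of an open-label trial with a patient-reported endpoint. The data are also at risk. If nobody collects PRWE from those who leave before treatment, no later analysis plan can recover it, and recruitment has been under way since March 2024.

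**Working it through.** **Step 1. Place the window.** Consent, then envelope assigned and opened at enrolment (16b, 16c), then waiting list or physiotherapy appointment (16c), then treatment. The replacement rule in 18b covers the stretch up to treatment. All of that stretch after the envelope is opened lies after randomisation.

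**Step 2. Follow one leaver through each analysis.**
- Primary endpoint: 6 months from treatment start. There is no start, so no assessment date.
- Visits at 3 and 12 months: the same.
- Survival: time zero is treatment start. There is no start, so no time at risk.
- Dropout clause in 18b: data collected before dropout are kept. For this person those are baseline data only.
- Imputation (20c): it can help only if the person is still in the dataset, which no section states.

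**Step 3. Size of the bias.** Let w be the share of one randomised arm that is replaced, and g the gap in mean 6-month PRWE between starters (m_s) and leavers (m_w), had leavers been followed. Assume replacements resemble starters.

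- Mean of the full randomised arm: (1 − w)·m_s + w·m_w
- Mean of the arm after replacement: m_s
- Bias in that arm: w·(m_s − m_w) = w·g
- Bias in the treatment difference: w·g for surgery minus w·g for exercise

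Inputs from the sample size section (item 14): MCID 14, SD 24, 70 per arm. Both w and g are assumptions, since the protocol gives neither. Withdrawal is placed in one arm only, which does not allow for any cancellation between arms. The standard error is 24 × √(2/70) = 4.06. The last column is the two-sided false-positive rate when the true difference among all randomised is zero and the nominal level is 0.05 (normal approximation).

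| Share w | Gap g | Replaced to obtain 70 starters, 70/(1 − w) − 70 | Bias w·g | Share of 14 | False-positive rate |
|---|---|---|---|---|---|
| any | 0 | – | 0 | 0% | 0.050 |
| 5% | 5 | 3.7 | 0.25 | 2% | 0.050 |
| 10% | 10 | 7.8 | 1.0 | 7% | 0.057 |
| 20% | 14 | 17.5 | 2.8 | 20% | 0.106 |

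If w·g is the same in both arms, the bias is zero whatever its size in each.

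**Step 4. Is replacement needed for power?** First the plan's own figure. With difference 14, SD 24, 80% power and two-sided 0.05, n = 2 × (1.960 + 0.842)² × 24²/14² = 46.1, so 47 per arm by the normal approximation and 48 by the t-test. The stated 64 is not reproduced. It would follow from SD 28 with a difference of 14. The step from 64 to 70 implies a loss of 1 − 64/70 = 8.6%.

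Now suppose 14 of 70 per arm have no outcome, leaving 56.
- SD 24: standard error 24 × √(2/56) = 4.54; 14/4.54 − 1.96 = 1.13; power about 87%.
- SD 28: standard error 28 × √(2/56) = 5.29; 14/5.29 − 1.96 = 0.69; power about 75%.

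On the stated inputs the trial does not need replacement to reach 80%. If the SD behind the 64 was really 28, a loss of that size would take it below 80%.

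**The case against.** The strongest reply is that the protocol never says replaced participants are dropped from the analysis. Replacement can mean recruiting one more person to keep numbers up, and that alone does not breach ITT. The protocol declares ITT, keeps data collected before dropout and plans imputation, and an analysis plan that is not shown could define the set. This stands in part: exclusion is an inference, not stated text. It is a strong one, because the rule is stated outright, the retained data are baseline only, and every outcome is timed from an event these people never have. If the benign meaning is intended, the protocol needs a sentence saying so and a follow-up date for non-starters.

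Three stronger readings are tempting, and the documents do not support them.
- **That the surgical arm loses more people.** Only surgery has a named waiting list, but exercise participants also wait to be contacted and booked. No waiting times or withdrawal rates are given. Unequal loss is plausible, but its direction and size are unknown.
- **That a replacement inherits the leaver's allocation.** The protocol does not say how a replacement is allocated. Drawing a fresh envelope is an equally open reading.
- **That the bias is large.** Gaps of 15–20 points can be imagined, but they exceed the protocol's own MCID and have no source. A fair range starts at zero.

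It is also true that someone who withdraws consent, as item 26a allows at any time, cannot be sent questionnaires. Not every missing outcome can be recovered.

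**Conclusion.** The point holds as a conflict between a stated rule and a stated principle. Following the rule, people who leave after randomisation have no defined 6-month PRWE or survival time, and the arms are topped up with others. The probable result is an analysis of those who were randomised and started treatment, although the protocol stops short of saying so.

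The size cannot be known from the document. With assumed shares of 5–20% in one arm and gaps of 5–14 points, the bias is 0.25 to 2.8 PRWE points, or 2% to 20% of the MCID. It is zero if leavers and starters have the same prognosis, or if share times gap is equal in both arms. Confidence is high on the rule, its timing and the missing time origin. It is lower on exclusion, and there is no basis for a claim about direction.

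**What to change.** 1. Restrict replacement to people who leave before the envelope is opened.
2. State that any extra recruit takes the next randomised envelope, and that extra recruitment never removes a randomised participant from the ITT set. Analyse everyone randomised in the allocated arm.
3. Separate declining treatment from withdrawing consent to follow-up. Ask those who only decline treatment for PROMs by the mail route already in 18b. Treat outcomes of those who withdraw consent as missing under the planned imputation.
4. In the ITT survival analysis, use one time origin, randomisation, for both arms.
5. Prespecify the date of the 6-month PRWE for non-starters, and add a sensitivity analysis timed from randomisation for everyone, so that the result does not rest on a mixture of two time origins.
6. Report the number of replacements since March 2024 by arm, and include the replaced people in the ITT set.

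The cost is a few sentences, some mailed questionnaires and a few more missing values. On the stated inputs, 56 per arm with outcomes would still give about 87% power. That reassurance depends on the SD of 24. The stated 64 per arm does not follow from the stated inputs; this is a separate issue and should be settled on its own.

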### Data management {19} and confidentiality {27}

Data is handled and stored in accordance with the ethical permits and the General Data Protection Regulation (GDPR). Data from the CRFs and PROM questionnaires are transferred to secure electronic databases at the South General Hospital, Skåne University Hospital, Karolinska Institutet, and Lund University. Participants are assigned pseudonymized serial numbers, and only the researchers responsible for the trial have access to the data files and the decoding key. Data are analysed anonymously, and all results are presented at group level. To ensure data quality, researchers independent from the study team will cross-check the transferred data for errors before both interim and final analyses.

### Plans for collection, laboratory evaluation, and storage of biological specimens for genetic or molecular analysis in this trial/future use {33}

N/A. No biological specimens are collected as part of this trial.

## Statistical methods

### Statistical methods for primary and secondary outcomes {20a}

For descriptive analysis, categorical data is presented as frequencies and percentages, whereas ordinal or skewed data is presented as median (IQR) and normally distributed continuous variables as mean (SD). For the primary endpoint, comparison between partial wrist denervation, and the patient education and exercise therapy program, the Wilcoxon signed-rank test will be used for paired data, and the Mann–Whitney *U*-test will be applied for unpaired data when the data are non-normally distributed or ordinal.

*T*-tests will be employed for changes in continuous data that follow a normal distribution, while the chi-square test will be used for categorical data. Normality will be assessed by the Shapiro–Wilk test. Generalized estimating equations (GEE), adjusted for age, sex, pain catastrophizing, operated dominant hand, SLAC/SNAC OA classification according to Watson and Vender [3, 4], and treatment site (Stockholm or Malmö), will be used for analysis of differences between groups regarding longitudinal data with repeated measurements. A robust estimator covariances matrix will be used. The working correlation matrix is selected according to the lowest Quasi-likelihood under Independence Model Criterion (QICC), and linear models will be used for all variables. Kaplan–Meier analysis will be performed to generate survival curves and Cox regression to compare differences in survival at 12-month post-intervention. *P*-values < 0.05 are considered significant.

Statistical analyses will be conducted following the intention-to-treat (ITT) principle. A secondary per-protocol (PP) analysis will be performed as a sensitivity analysis to assess the robustness of the findings. If a participant requires additional wrist surgery during follow-up or has a major trauma or other disease affecting the included hand, analyses will be conducted according to ITT up to that event. Data collected after such an event will not be analysed.

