### Sample size {14}

The reported minimal clinically important difference (MCID) of PRWE is 14 points (out of 100) based on previous research [41]. To show a difference of at least 14 points in PRWE score between partial wrist denervation and the education and exercise therapy program (SD 24) [13], after 6 months, 64 participants are required in each treatment arm. The power will be 80% (*p* < 0.05). To account for lost to follow-up, we aim to include 140 participants in total, 70 per treatment arm.

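### The primary PRWE comparison switches between a mean test and a rank test on a normality result, sits beside a GEE of unstated rank, and never adjusts for baseline PRWE

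*Protocol article*

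**What the plan says.** All references are to the protocol article.

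- **Endpoint** (Primary outcome measure, under Outcomes {12}): "The primary outcome is the change of PRWE score [31] with a primary endpoint at 6 months following the start of the intervention".
- **Target** (Sample size {14}): "To show a difference of at least 14 points in PRWE score between partial wrist denervation and the education and exercise therapy program". The SD and size follow as "SD 24) [13], after 6 months, 64 participants are required in each treatment arm", at 80% power. The text does not say whether 24 is the SD of the 6-month score or of the change.
- **Tests** (Statistical methods {20a}): for the primary endpoint, Mann–Whitney is given for unpaired data that are non-normal or ordinal, and t-tests for changes that are normally distributed. The selector is "Normality will be assessed by the Shapiro–Wilk test". In the same sentence as the primary comparison, "the Wilcoxon signed-rank test will be used for paired data". None of these tests carries a covariate.
- **Model** (same section): a GEE for between-group differences in repeated measurements, "adjusted for age, sex, pain catastrophizing, operated dominant hand", with OA classification and site. Baseline PRWE is not in the list. The section does not say how the GEE ranks against the tests.
- **Data available** (Plans for assessment and collection of outcomes {18a}): the PROMs "are collected at baseline, 3, 6, and 12 months after intervention".

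**The concern.** A confirmatory superiority trial needs one analysis that yields one estimate and one p-value for its primary endpoint. Here the outcome data decide whether the result concerns a difference in mean change or a difference in ranks. Only the first can be read directly against 14 points. A second, adjusted analysis of the same 6-month contrast stands beside it without a label.

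Baseline PRWE is likely to be among the best predictors of 6-month PRWE. A change score uses it with a fixed weight of one, which is inefficient unless the correlation is very high.

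Two other parts of the protocol make this matter. The Discussion ties a firm conclusion to this comparison: if denervation is not superior, it should no longer be considered for wrist OA. And the interim analyses {21b} re-check the variance behind the sample size at 50 and 100 participants. Until one primary analysis is named, it is unclear whether that means the variance of the score, of the change, or of the residual.

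**Working it through.** **1. The plan's own figure.** Inputs: difference 14, SD 24, power 80%, alpha 0.05 (two-sided assumed).

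n per arm = 2(1.96 + 0.842)² × 24² / 14² = 47 (48 with the exact t-test).

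The stated 64 is not reproduced. At 64 per arm, power = Φ(14√(64/2)/24 − 1.96) = Φ(1.34) = 91%. The mismatch is a separate matter. Here it shows only that, on the stated inputs, the unadjusted comparison has power to spare.

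**2. Gain from baseline adjustment.** Let σ be the SD of PRWE, taken as equal at both times and in both arms, and r the baseline-to-6-month correlation. The documents give no r, so 0.3 to 0.7 is an assumption.

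- Variance of change: 2(1 − r)σ²
- Baseline-adjusted residual variance: (1 − r²)σ²
- Ratio: (1 + r)/2 = 0.65, 0.75, 0.85 at r = 0.3, 0.5, 0.7, a reduction of 35%, 25%, 15%

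**3. Power at 64 per arm**, from Φ(14√32/SD − 1.96).

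If 24 is the SD of the score:

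| r | SD of change | power | adjusted SD | power | n per arm for 80% (change v adjusted) |
|---|---|---|---|---|---|
| 0.3 | 28.4 | 80% | 22.9 | 93% | 65 v 42 |
| 0.5 | 24.0 | 91% | 20.8 | 97% | 47 v 35 |
| 0.7 | 18.6 | 99% | 17.1 | 99.6% | 28 v 24 |

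On this reading, comparing 6-month scores with no use of baseline has 91% power. At r = 0.3, subtracting baseline therefore does worse than ignoring it.

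If 24 is the SD of change, the unadjusted test has 91% at any r. The adjusted SD is 24√((1 + r)/2) = 19.3, 20.8, 22.1, giving 98%, 97%, 95% at r = 0.3, 0.5, 0.7.

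**4. The normality switch.** This was simulated with 64 per arm and 4,000 null trials per setting, for normal, bounded (0–100) and skewed outcomes at r = 0.3, 0.5 and 0.7. Shapiro–Wilk was applied to change in each arm at 0.05, and a rejection in either arm led to Mann–Whitney.

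- Type I error of the two-stage rule: 4.7–6.0%. The t-test alone in the same runs: 4.6–5.9%. The two never differed by more than 0.4 points, and the simulation standard error is about 0.3 points.
- With truly normal changes, the switch to Mann–Whitney occurred by chance in about 10% of trials (expected 1 − 0.95² = 9.75%).
- Reporting the smallest p from t-test, Mann–Whitney and a baseline-adjusted model: 8.0–9.3%.

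**5. Could the GEE already supply the adjustment?** Baseline is not a listed covariate. If baseline PRWE entered as one of the repeated outcomes with an unconstrained arm-by-visit mean, the 6-month contrast would be the difference in mean change again, without the gain in step 2.

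**The case against.** The strongest defence is that the section does separate roles, though without labels. The simple tests are tied to the primary endpoint and the GEE to longitudinal data. The t-test and Mann–Whitney are not free alternatives, because a stated rule picks one. An unadjusted change score is unbiased under randomization, so baseline adjustment is a matter of efficiency. A statistical analysis plan that is not at hand may rank the GEE. All of this is fair, and it lowers the severity. It does not remove the point: the protocol itself fixes the normality switch, the unadjusted tests and a covariate list without baseline PRWE.

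The gain is also not universal. With the skewed outcomes simulated, Mann–Whitney matched the baseline-adjusted model at r = 0.5 (96.5% v 96.3% power), though not at r = 0.3 (84.5% v 93.1%). That is a reason to keep the rank test as a sensitivity analysis.

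A reader might infer more than the documents support:

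- **That type I error is inflated.** The switch alone leaves it near 5%. The 8–9% figure needs someone to report the smallest p-value, which the protocol nowhere proposes, and it includes a baseline-adjusted model the protocol does not have. Data analysts are also to be blinded {17a}.
- **That the trial is underpowered.** On the stated inputs it has about 91% at 64 per arm. Unadjusted power falls to about 80% or below only if 24 is the score SD and r is about 0.3 or less.
- **That the covariates distort the treatment effect.** The exercise arm has no operated hand, but the list serves both arms, so dominance of the affected side is evidently meant. Pain catastrophizing is measured at baseline, and nothing says follow-up values will be used. Both are wording points.
- **That the signed-rank test or QICC selection corrupts the primary result.** The first reads as a misplaced within-arm analysis. The second is a pre-stated rule used with robust standard errors.

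**Conclusion.** The point holds as a should-fix. The primary estimand depends on a Shapiro–Wilk result, one branch gives no mean difference to compare with the MCID, the rank of the GEE is unstated, and baseline PRWE is collected but not adjusted for.

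The cost is precision: an unadjusted change score carries 1/0.65 = 1.54, 1/0.75 = 1.33 or 1/0.85 = 1.18 times the variance of the adjusted comparison at r = 0.3, 0.5 or 0.7. In power at 64 per arm this ranges from about 13 points (score SD 24, r = 0.3) to under 1 point (score SD 24, r = 0.7). These sizes rest on an assumed r, equal SDs at the two times, and roughly normal outcomes. Which power row applies depends on what SD 24 measures, and the protocol does not say.

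**What to change.** 1. Name one primary analysis: a linear repeated-measures model or GEE of PRWE at 3, 6 and 12 months with arm, visit, arm-by-visit, baseline PRWE, site and the listed covariates, all taken at baseline. The primary result is the 6-month adjusted mean difference with 95% CI, read against 14 points.
2. Drop the normality pre-test for the primary endpoint. Keep Mann–Whitney on change as a labelled sensitivity analysis, and move the signed-rank test to within-arm description.
3. Reword the hand covariate as whether the affected wrist is on the dominant side, and state that pain catastrophizing is the baseline value.
4. Adjust each secondary outcome for its own baseline where one exists.
5. State whether SD 24 refers to the score or the change, so that the interim variance check is made on the matching quantity.

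The cost is wording. Every variable is already collected, and recruitment is expected to run to 2027, so the change can be made before allocation is revealed to the analysts. If it counts as a significant amendment, section {25} requires ethics approval and an update of the registration.
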